**Intervention**

*BA Intervention group*

Participants in the intervention group will receive BA treatment in addition to standard care. These participants will be offered 12 sessions of BA, which will be delivered twice weekly, in 30-minute sessions, for six weeks. Participants will be deemed to have received an adequate ‘dose’ of the intervention if they have attended 6 BA sessions over the 6-week period (i.e. 50%). The BA treatment will follow a treatment protocol based on previous trials of BA for depression [26], the COBRA trial protocol [27] and the National Institute for Health and Care Excellence recommendations for the frequency and duration of BA therapy [28]. Specific BA techniques that will be applied include the: identification of depressed behaviours; analysis of the triggers and consequences of depressed behaviours; monitoring of activities; development of alternative goal-orientated behaviours; scheduling of activities; and the development of alternative behavioural responses to rumination.

*TAU group*

Every participant in the control group will receive routine standard early intervention in psychosis services and no other specific intervention will be provided. Across sites, TAU is composed of case management and antipsychotic medication. Additionally, TAU may involve family support, psychosocial groups, vocational support, peer support as well as care for physical health. Multidisciplinary teams responsible for delivering standard care services usually consist of psychologists, psychiatrists, mental health nurses, occupational therapists, and social workers. The TAU condition will ensure appropriate, ongoing quality care for this group of young people. Young people at UHR status should receive care for at least 12 months and those with FEP for two years [22].

*BA training*

Eight clinicians will be recruited and trained to deliver the intervention. Each clinician will deliver the intervention to approximately five YPEEP participants. The clinicians will be trained in BA techniques using an academically accredited and established online “Professional Certificate in BA for Depression” program offered by the University of South Australia (facilitated by MJ and SD). The 10-week online training consists of five modules (the evidence base of BA; introduction to BA; assessment and mood monitoring; functional analysis; and activity scheduling).

The expected learning outcomes upon completion of the online training program are that the clinicians will acquire a sound understanding of the BA intervention, develop the relevant core skills, and demonstrate competency in BA delivery. Trainees are assessed using multiple choice questionnaires at the end of each module and via an assessment of an audio recorded Behavioural Activation Assessment and an Activity Schedule with a work colleague. Following the satisfactory completion of the training, clinicians will be supported through monthly, online clinical supervision sessions provided by the researchers who are experienced in teaching and supervising BA trainees.

*Intervention fidelity*

Intervention fidelity will be established via recording randomly selected treatment sessions and completing a fidelity checklist. Two sessions of BA treatment will be randomly chosen from each clinician and audio-recorded (with the clinician’s and participants’ prior consent) by the researchers to monitor fidelity to the treatment protocol. The fidelity checklist [29] will be used by two researchers, independently, to assess the clinician’s adherence to BA treatment protocol. The schedule of enrolment, intervention and assessments is shown in Figure 1.

Fig 1. Schedule of enrolment, interventions, and assessments

[figure not shown]

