**Study aim and objectives**

The overall aim will be to train at least eight clinicians in BA using an established University accredited online “Professional Certificate in BA for Depression” program and support them to deliver BA to improve depressive symptoms in YPEEP. Specifically, the objectives of the pilot trial are to:

1. Establish the proportion of YPEEP with clinically meaningful depression symptoms.
2. Establish the proportion of clinicians that complete the BA training and are deemed to be competent.
3. Determine the proportion of eligible participants approached who agree to consent to the research.
4. Determine the proportion of participants that complete baseline measures, complete BA treatment (attending for a minimum of six sessions over the six weeks), and complete follow-up measures (immediately post intervention and at 3 months follow-up).

Additionally, we will:

1. Establish clinicians’ fidelity to treatment.
2. Calculate preliminary efficacy of BA on clinical outcome measures.
3. Explore participants’ experiences of facilitating BA (clinicians) and receiving BA (YPEEP).

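### Each clinician's fidelity rating rests on two randomly drawn sessions, with nothing to spread them over the 12-session course or over clients

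*Protocol*

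**What the plan says.** Under Study aim and objectives, the protocol lists "Establish clinicians’ fidelity to treatment" among the additional aims, after the four numbered feasibility objectives. The method is in the Intervention fidelity section: "Intervention fidelity will be established via recording randomly selected treatment sessions and completing a fidelity checklist". The number is set there too: "Two sessions of BA treatment will be randomly chosen from each clinician and audio-recorded". The ratings are then used as follows: "The fidelity checklist [29] will be used by two researchers, independently, to assess the clinician’s adherence to BA treatment protocol".

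The BA Intervention group section gives the length of the course: "These participants will be offered 12 sessions of BA, which will be delivered twice weekly, in 30-minute sessions, for six weeks". It names six techniques, four of which are "analysis of the triggers and consequences of depressed behaviours; monitoring of activities; development of alternative goal-orientated behaviours; scheduling of activities". The other two are identifying depressed behaviours and developing alternatives to rumination. The protocol does not assign techniques to sessions or divide the course into phases. It also does not define the set of sessions from which the two are drawn, and it sets no condition on stage of treatment or on client.

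**The concern.** The rating is meant to describe how well a clinician keeps to the BA protocol as a whole. That protocol has distinct components. Besides the six techniques, the training has separate modules for assessment and mood monitoring, functional analysis, and activity scheduling. Trainees are examined on two different recorded tasks, an assessment and an activity schedule. So training requires evidence on more than one component, while the in-trial fidelity check guarantees no such spread.

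If both recordings fall in the same part of the course, they say nothing about how that clinician handled the rest. If both come from one client, they cannot separate the clinician's usual practice from the particulars of that client. The protocol's rationale includes the claim that non-specialist clinicians can deliver BA with high fidelity, and the pilot is to inform a full trial. A per-clinician rating with this gap is weaker evidence on that claim than the same two recordings could give.

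**Working it through.** The protocol gives no coverage or precision figure for fidelity, so there is none to reproduce.

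**Inputs**
- 8 clinicians (BA training section), 2 rated sessions each (Intervention fidelity section): 8 × 2 = 16 recordings.
- 12 sessions offered per participant (BA Intervention group section) and 30 participants in the BA arm (Sample size section): 30 × 12 = 360 sessions. Share rated: 16/360 = 4.4%.
- Clients per clinician: the BA training section says about five, but 8 × 5 = 40 does not fit an arm of 30, and 30/8 = 3.75. I use 4 and 5; the choice hardly matters.
- Assumptions: a simple random draw without replacement from all of a clinician's sessions, equal phases, full attendance, and independence between clinicians.

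**Both sessions in the same phase.** With N sessions per clinician in k equal phases, P = k × C(N/k, 2) / C(N, 2).

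| Phases | 4 clients (N = 48) | 5 clients (N = 60) |
|---|---|---|
| 2 | 2 × 276/1128 = 0.489 | 2 × 435/1770 = 0.492 |
| 3 | 3 × 120/1128 = 0.319 | 3 × 190/1770 = 0.322 |
| 4 | 4 × 66/1128 = 0.234 | 4 × 105/1770 = 0.237 |

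For two halves, the expected number of clinicians with one half unrated is 8 × 0.489 = 3.9, with SD √(8 × 0.489 × 0.511) = 1.4. The count is therefore quite variable: the binomial chance of at least 4 of 8 is 0.61. With three or more phases the chance of sharing a phase is lower, but two sessions then leave at least one phase unrated for every clinician.

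**Missed late sessions.** Attending 6 of 12 sessions counts as an adequate dose, so the late half may be thinner. If each of four clients attends all six early sessions and only two late ones, P = (C(24, 2) + C(8, 2)) / C(32, 2) = (276 + 28)/496 = 0.61.

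**Both sessions from one client.** After the first session is drawn, 11 of the remaining N − 1 belong to the same client: 11/47 = 23% with four clients, 11/59 = 19% with five.

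**Coverage across the trial.** With four clients, one clinician's two sessions both fall in a given half with probability 276/1128 = 0.245. The chance that all 16 recordings fall in one half is 2 × 0.2447^8 = 0.000026, about 1 in 39,000.

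**With the draw split by half.** Where a clinician has sessions in both halves, the same-half probability goes from about 0.49 to 0, with the same 16 recordings.

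**The case against.** The strongest reply is that the protocol has no phases. The techniques are listed without sequence, and some, such as monitoring and scheduling activities, could recur in most sessions. Two sessions from one half would then lose little. This stands, and it is why the 49% must be stated as conditional.

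Second, the wording does not exclude a stratified random draw, and a fidelity procedure could supply the detail. That is fair. But the protocol fixes the number of sessions and the random choice and states no spread, and a simple draw is the natural reading.

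Third, both halves would almost certainly be sampled across the trial, and no decision in the protocol turns on one clinician's rating. Random choice, two independent raters, assessed training and monthly supervision are real safeguards. This limits the point to per-clinician coverage, although the stated purpose of the checklist is to assess the individual clinician's adherence.

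Fourth, two 30-minute sessions, however drawn, need not show all six techniques. True: the fix improves coverage and does not complete it.

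A reader might also infer that clinicians know which sessions are scored, because only selected sessions are recorded and consent is obtained beforehand. The protocol does not say when the clinician learns of the selection, and consent could be general. Nor does it give any basis for saying that such ratings would run high.

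**Conclusion.** The point holds at modest weight. The fidelity draw leaves each clinician's coverage of the course and of clients to chance, although the same effort could secure a spread. If content differs between the two halves of the course, about 49% of clinicians (about 4 of 8 expected) would be rated on one half only. The chance of sharing one phase is about 32% with three phases and 24% with four. The chance that both recordings come from one client is about 19% to 23%. These figures assume a simple random draw, equal phases and full attendance, and the first rises if late sessions are missed.

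Two stronger conclusions are not supported. One is that about half the clinicians will in fact be rated on one phase of BA: the figure is an expectation under an assumed split. The other is that the depression result could not be interpreted. Fidelity is an additional objective, it is not among the feasibility outcomes in the Evaluation section, and the Sample size section already disclaims power to detect group differences.

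**What to change.** Keep two recordings per clinician. Draw one at random from sessions 1–6 and one at random from sessions 7–12, and take them from different participants where the clinician has more than one. State a fallback: if no late session takes place for a clinician, draw at random from the sessions that are available, and report that this was done.

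The number of recordings (16), the checklist and the two raters are unchanged. The only cost is writing and applying the fallback rule, which is needed because some participants may stop before the second half. No extra recording is needed.

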**Evaluation**

*Feasibility*

The study feasibility outcomes will be evaluated by calculating a) the proportion of YPEEP with clinically meaningful depression symptoms; b) the proportion of clinicians that complete the BA training and the proportion deemed to be competent; c) the proportion of eligible participants approached who agree to consent to the research; d) the proportion of YPEEP participants that complete baseline measures, complete BA treatment (attending for at least six sessions), and complete follow-up measures (immediately post intervention and at 3 months follow-up).

*Experiences of the intervention/trial*

Semi-structured interviews will be undertaken with a subset of clinicians (minimum of 4) and YPEEP participants (minimum of 12) to explore their experiences of involvement in the pilot trial. Interviews will be conducted with clinicians to gain insight into their experiences of delivering BA therapy and the BA training/supervision. Interviews with YPEEP participants will focus on their experiences of engaging in the BA program and participating in the study. General topic areas (for YPEEP and clinicians) will include: what worked; what did not work; what could be done differently; what could be improved; and what were the facilitators and barriers to engaging with/facilitating the intervention. The young person will be offered the option of having a parent/guardian or support person present in the interview, if desired. The interviews will be conducted by an experienced researcher (in-person or by phone) and are anticipated to last no more than 30 minutes. Data saturation will be determined in relation to the range and diversity of experiences; based on attendance at the BA sessions, engagement with the trial more generally and clinical outcomes. Additional interviews may be conducted so to achieve data saturation.

**Preliminary intervention effects (primary and secondary outcomes)**

The primary outcome will be the assessment of depressive symptoms. The secondary outcome will be the assessment of negative symptoms, overall psychiatric symptoms, medication side effects, and functioning. Outcome measures will be completed at baseline (0 weeks), immediately post-intervention (6 weeks) and 3-months post-intervention.

Depressive symptoms: The depressive symptoms will be measured with Calgary Depression Scale for Schizophrenia (CDSS) [30]. The CDSS is a 4-point Likert type scale (0, absent; 1, mild; 2, moderate; 3, severe) with nine items. It is considered to be a reliable scale, with high internal consistency (Cronbach's alpha= 0.855), and the CDSS is suitable for evaluating symptoms of depression in people at clinical high risk for psychosis [31], including young people [32].

Negative symptoms: The Scale for Assessment of Negative Symptoms (SANS) [33] will be used to assess the negative symptoms of schizophrenia. SANS is 6-point Likert type scale (from 0, none to 5, severe), comprised of five scales each of which assess aspects of negative symptoms; alogia, affective blunting, avolition-apathy, anhedonia-asociality, and attentional impairment. The SANS has demonstrated a high level of reliability, with an overall Cronbach’s alpha ranging from 0.89 to 0.95 and global intraclass correlation coefficient (test-retest reliability) of more than 0.82 in different studies [33-35].

Psychiatric symptoms: The Brief Psychiatric Rating Scale (BPRS) [36] is a 7-point Likert type scale (1, not present-7, extremely severe) which is used to rate psychiatric symptoms such as anxiety, depression, and psychoses. The BPRS has demonstrated good reliability, with overall Cronbach’s alpha value of 0.69 [37] and an overall intra-class correlation of R = 0.78 (p< 0.001) [38].

Medication side effects: The Glasgow Antipsychotic Side-effect Scale (GASS) [39] is 4-point Likert type scale (from 0 point, never to 3 point, everyday) containing 22 items. It is a self-report rating scale which measures an individual’s viewpoint about side effects of antipsychotic medication. The GASS has demonstrated a good test-retest reliability (kappa value=0.72) [39] and internal consistency reliability with Cronbach's alpha ranging from 0.793 to 0.903 [40-42].

Functioning: The Work and Social Adjustment Scale (WSAS) [43] will be used to assess the impact of early/emerging psychosis on various aspects of functioning. The WSAS is a five item self-reported, nine-point Likert scale. It measures how illness impacts on (1) ability to work, (2) home management, (3) social leisure, (4) private leisure and (5) ability to form and maintain close relationships. The Cronbach’s alpha ranges from 0.70 to 0.94 and the overall test–retest correlation score is 0.73 [44].

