**Materials and methods**

**Study design**

The feasibility and acceptability of delivering BA to YPEEP clients will be assessed using a pilot controlled clinical trial with a two-arm parallel-group design. This pilot trial protocol is registered with the Australian New Zealand Clinical Trials Registry (ref no. ACTRN12622000756729). The ‘Standard Protocol Items: Recommendations for Interventional Trials’ (SPIRIT) [20, 21] is used to guide the presentation of the current study protocol (see S1 File: Completed SPIRIT checklist). The pilot trial will be conducted in accordance with IHI Good Clinical Practice guidelines. A trial steering committee will be convened to oversee and guide the research as needed.

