**Sample size**

There has been some degree of ambiguity about sample size requirements for feasibility studies and there are no previous studies which have evaluated BA in YPEEP which could be used to guide this estimate. Therefore, our sample size estimation will be based on recommendations from the literature that feasibility studies ought to aim for sample sizes of between 24 and 50 participants [23, 24]. Furthermore, a systematic review of UK registered feasibility studies reported the median sample size with continuous outcome measures to be 30 participants per group [25]. Based on this guidance, our target sample size is 60 participants (30 in each group). This estimate will facilitate the generation of information about sample size requirements for a subsequent full-scale trial and is not intended to be sufficiently powered to detect statistically significant differences in outcomes between groups.

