**Data collection and management**

The trained research assistant will facilitate the data collection process. With prior written consent, participant demographic information will be collected through the early psychosis service at the study site. For the primary (depressive symptoms) and secondary outcomes (negative symptoms, overall psychiatric symptoms, medication side effects, functioning), the data will be collected at baseline, 6 weeks post-intervention and 3 months post-intervention respectively. There are no plans for specific activities to promote participant retention other than the BA intervention being facilitated by participants’ regular clinician and by keeping participant burden to a minimum. With participants’ permission, all outcome data will be collected and analysed from participants who discontinue the study or deviate from the intervention protocol.

The qualitative interviews will be audio-recorded and will subsequently be transcribed. The researcher conducting the interview will ensure that there is no patient identifiable information (e.g. names, addresses) on the audio recording. A professional transcription service with appropriate confidentiality and data security policies will be engaged to transcribe digital recordings of the interviews. Transcriptions will be de-identified by the research team to ensure anonymity. Subsequently, audio-recordings will be securely destroyed. Data will be stored securely on the university’s server and files will be password protected. Only the relevant members of the research team will have access to these files. In accordance with NHMRC guidelines for clinical trials, data will be retained for 15 years and then securely destroyed. Data will be managed in accordance with the National Statement on Ethical Conduct in Human Research and the Charles Darwin University Research Data Management Procedures [45].

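### The only outcome labelled primary is depressive symptoms on the CDSS, tested at P < 0.05, although the numbered objectives are feasibility and the trial was not sized for between-group differences

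*Protocol*

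**What the plan says.** The Protocol's *Study design* section gives the purpose: "The feasibility and acceptability of delivering BA to YPEEP clients will be assessed using a pilot controlled clinical trial". *Study aim and objectives* numbers four objectives for the pilot, and all are feasibility proportions. The third is typical: "Determine the proportion of eligible participants approached who agree to consent to the research". Efficacy comes in a separate list of additional aims: "Calculate preliminary efficacy of BA on clinical outcome measures".

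*Sample size* sets 60 participants, 30 per group, from published guidance on feasibility studies. It adds that this number "is not intended to be sufficiently powered to detect statistically significant differences in outcomes between groups".

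*Evaluation* (Feasibility) lists outcomes (a) to (d), which match the four objectives, and ranks none of them. The next section, *Preliminary intervention effects (primary and secondary outcomes)*, says "The primary outcome will be the assessment of depressive symptoms" and names the CDSS as the instrument. *Data collection and management* repeats the label: "For the primary (depressive symptoms) and secondary outcomes", followed by the other clinical domains.

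*Statistical analyses* plans a GEE over three time points for the preliminary effects. If the overall treatment effect is significant, t-tests follow between arms on the primary and secondary measures at both follow-ups. The level is P < 0.05 in all tests. Feasibility data are summarised descriptively.

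**The concern.** The outcome hierarchy runs against the objectives. The one outcome called primary serves an additional aim, and none of the four main objectives has an outcome with that label. The planned between-arm testing after baseline falls wholly on measures for which the trial, by its own account, was not sized.

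The label matters because readers normally look first to the primary outcome. A non-significant CDSS result could be taken as evidence against BA, although the trial was not designed to show an effect. A chance significant result could be reported as efficacy on the primary outcome. The feasibility proportions, which the numbered objectives ask for, could come second in the report. A separate statistical analysis plan may exist, but the hierarchy is already fixed in the protocol.

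**Working it through.** **1. The plan's own figure.** The target comes from a cited median of 30 per group: 30 × 2 = 60. This reproduces. No effect size, SD or power is given, so there is no power claim to check. The question is how far 30 per arm can inform on the outcome named primary.

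**2. Inputs.**
- From the protocol: n = 30 per arm and alpha 0.05.
- Assumed, because the protocol gives none: two-sided tests, standardised effects d, 20% loss (24 per arm), and baseline-to-follow-up correlations r.

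**3. Unadjusted t-test at one follow-up.** The non-centrality is d × √(n/2), with 2n − 2 degrees of freedom.
- For n = 30 and d = 0.5: 0.5 × √15 = 1.94 on 58 df.
- For n = 30 and d = 0.3: 0.3 × √15 = 1.16 on 58 df.

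| Per arm | d = 0.3 | d = 0.5 | d = 0.8 |
|---|---|---|---|
| 30 | 21% | 48% | 86% |
| 24 (20% loss assumed) | 17% | 40% | 77% |

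The normal approximation gives nearly the same at n = 30: 21%, 49% and 87%.

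**4. Using baseline.** The residual SD becomes √(1 − r²), which is 0.866 at r = 0.5 and 0.714 at r = 0.7. Power at d = 0.5 is then as follows (t-based, with the normal approximation in brackets where used).

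| Per arm | r = 0.5 | r = 0.7 |
|---|---|---|
| 30 | 59% (61%) | 76% (77%) |
| 24 | 50% | 66% |

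This approximates what a model using baseline could gain. It is not a calculation for the planned GEE, whose model terms and correlation structure the protocol does not give.

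**5. Smallest effect with 80% power.** The normal approximation is (1.96 + 0.84) × √(2/30) = 0.72 SD unadjusted. With baseline at r = 0.5 and no loss it is 0.63 SD. Unadjusted, 80% power at d = 0.5 would need 126 participants before dropout, about twice the planned 60.

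**6. Precision.** The 95% half-width is t(0.975, 58) × √(2/30) = 2.002 × 0.258 = 0.52 SD. With 24 per arm it is 2.013 × 0.289 = 0.58 SD. An observed difference of exactly 0.5 SD would carry an interval from −0.02 to 1.02 SD.

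**7. Precision of the feasibility proportions at the same N.** The half-width is 1.96 × √(p(1 − p)/n).
- Follow-up completion, n = 60: ±13 points at p = 0.5 and ±10 at p = 0.8.
- BA completion, n = 30: ±18 and ±14 points.
- Clinician outcomes, n = 8: about ±35 and ±28 points, and the approximation is rough at that size.

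Making the feasibility outcomes primary therefore needs no change in sample size.

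**The case against.** The best defence is scope. Feasibility is set out first, and the depressive-symptom sentence then stands under a heading about preliminary intervention effects. On that reading, primary means primary among the clinical scales. The repetition in *Data collection and management* only sets assessment times for the same measures. *Statistical analyses* again calls the effects preliminary, and *Dissemination* commits to the CONSORT extension for pilot and feasibility trials. Each numbered objective has a matching measure and a descriptive analysis. Only the label is missing.

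Much of this stands. The narrow reading is plausible and may be what the authors meant. But the text does not state it, the label recurs outside that heading, and no feasibility outcome is ranked. The P < 0.05 testing with its gated t-tests remains on either reading.

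A reader might infer four stronger points that the document does not support:
- **That the protocol says it cannot test clinical outcomes.** It says only that the size was not intended to give sufficient power, and it plans tests.
- **That the trial's success, or the programme's future, hangs on the CDSS.** No success, progression or stopping rule uses it.
- **That a non-significant result is more likely than not under a moderate effect.** This holds for the unadjusted comparison at d = 0.5, but not if baseline is used with r = 0.5 and no loss. At d = 0.8 even unadjusted power is 86%.
- **That the registry entry has the same fault.** It was not available for this review.

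**Conclusion.** The point holds as an inconsistency in the outcome hierarchy and in the testing attached to it. The objectives and design purpose are feasibility, and the sample size is disclaimed for between-group differences. The only primary label nevertheless goes to depressive symptoms on the CDSS, which is tested at P < 0.05.

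Under the assumed effects, the unadjusted comparison has about 48% power at 0.5 SD and 21% at 0.3 SD. Using baseline at r = 0.5 without loss raises the first figure to 59–61%. The interval of about ±0.52 SD, unadjusted, is too wide to tell no effect from a moderate one. The textual conflict depends on none of these assumptions.

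Measuring the CDSS is legitimate, and so is a target of 60. The faults are the label and the significance-gated tests. The heading and the reporting commitment soften the conflict but do not remove it.

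**What to change.** 1. In *Preliminary intervention effects* and *Data collection and management*, name the feasibility proportions (a) to (d) under *Evaluation* (Feasibility) as the primary outcomes. Name the CDSS as the main clinical secondary outcome, with SANS, BPRS, GASS and WSAS as other secondary outcomes.
2. In *Statistical analyses*, report the CDSS and the other scales as between-arm differences with 95% confidence intervals. Remove the follow-up t-tests that depend on a significant GEE result, and state that no efficacy conclusion will be drawn from P values.
3. Check the registry entry and align it only if it differs.

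The cost is a wording amendment, with the ethics approval and any registry update that the protocol already requires for modifications. Sample size, data collection and participants are unaffected. The trial gives up an efficacy claim for which its own sample-size section says it was not sized.
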